### Control condition

In the control condition the usual activities of participants continue. No intervention actions are undertaken. Some study sites use a waitlist design to allow participants in the control condition to receive the intervention programme after data collection has terminated. Study sites might provide incentives to control participants such as money, groceries, keeping of study devices after completion of the data collection.

### Study population and eligibility to participate in the study

All participants who provide informed consent are enrolled in the study. We aim to include 1750 participants in total. Each study site allocates at least 125 participants to the intervention condition and 125 participants to the control condition. Detailed numbers of participants per study site are presented in Table 1. Study sites might apply randomization at individual or cluster level to create intervention and control condition.

Study participants are included if they: (i) are aged ≥ 18 years old, (ii) are in a vulnerable situation (e.g. unemployed, low income, single parents, parents with dependent children, seniors (65 +) with dependency conditions, seniors (65 +) living alone, people with disabilities attended by social services, belonging to a minority, migrant situation), (iii) living in energy poverty conditions, and (vi) belonging to the recruitment sites identified by the local partners for the study. The research assistant recruits potential participants in collaboration with local agencies that work in the catchment area. Together they determine energy poverty conditions (criterion iii), based on their knowledge of and experience with the target population. The primary indicators suggested by EU Energy Poverty Observatory (EPOV) are used as guideline to assess the energy poverty status. EPOV established the following criteria:i.arrears on utility bills;ii.low absolute energy expenditure (below half of the national median (M/2));iii.high share of energy expenditure in income (double of the national median share of energy expenditure in income (2 M)) andiv.inability to keep home adequately warm [26].

Persons are not eligible to participate if they have previously been beneficiaries of a previous similar intervention, cannot adequately participate in the intervention actions proposed in the study site (e.g. intellectual disabilities, severe language limitations) or are illegally connected to the electricity grid.

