### Study design

A controlled trial is performed with an intervention condition and a control condition (i.e. no specific programme to address energy poverty is applied) in six study sites in Europe. Measures are taken at baseline (T0), at 6 months (T1), at 12 months (T2) and 18 months after baseline (follow-up; T3) in both research groups. In addition, in the intervention condition additional frequent monitoring of health and housing conditions takes place. Moreover, qualitative interviews with a subsample of participants undergoing the intervention condition take place near the beginning of the intervention (3–6 months) and after termination of the intervention (15–18 months).

The WELLBASED intervention programme targets adults ≥ 18y in vulnerable situations, living in energy poverty conditions that belong to one of the study sites. An overview of study sites and the target population is presented in Table 1. Local organisations (e.g. the social services department or an non-governmental organisation (NGO) that supports vulnerable groups) or the local research team, depending on study site, select eligible individuals. Recruitment of study participants and baseline data collection is scheduled to commence in autumn 2022. Potential participants in the catchment area of an intervention or control site receive information about the study and an invitation to provide informed consent to join the study by the study site team. Generally, in each selected household, the person who is considered responsible for the accommodation or best placed to provide the information is invited to join the study and to complete questionnaires. This participant is also invited to participate in health data collection and, when applicable, to join qualitative interviews at a later stage. In some cases more than one person per household may be invited to join the study. Participants only join the study after they have provided informed consent. Study participants, intervention providers and research assistants are not blinded due to the nature of the intervention. The study is performed in accordance with the capacity, organizational and contextual factors of each of the six participating cities, as described below.

**Table 1 Tab1:** Study site characteristics

STUDY SITE	RECRUITMENT OF PARTICIPANTS	
	**TARGET GROUP**	**NUMBER OF PARTICIPANTS**

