### Data management and analysis

Data from all study sites are pseudo anonymized and combined in an online data platform (handled by INCLIVA). Erasmus University Medical Center is responsible for analysis and reporting. As the project will collect health-related data, special attention is attributed to the role of each partner in terms of controllers and processors, and to the organizational and technical measures to be put in place to ensure General Data Protection Regulation (GDPR) compliance. In addition, the risks associated to data processing will be defined in the Data Protection Impact Assessment (art. 35 GDPR) to be evaluated together with the Controllers’ Data Protection Officers. The data management plan includes procedures for ensuring a high-quality data standard, according to the FAIR principles: Findability, Accessibility, Interoperability, and Reusability [41]. All data are handled confidentially and scientific data are stored anonymously.

Descriptive statistics are used to describe participant characteristics in each study site and in the total study population, and to describe implementation outcomes in the study sites. Differences between T0, T1, T2 and T3 measurements are evaluated using multilevel linear regression analyses for continuous outcome variables and multilevel logistic regression analyses for dichotomous outcome variables. Interaction tests are performed for age, gender, living situation and education level to evaluate effects in subgroups. Statistical analyses are repeated for each study site separately. We consider a *P*-value of 0.05 or lower to be statistically significant. Analyses are performed according to the ‘intention to treat’ principle. An additional per protocol analyses is performed to evaluate the impact of the dose of the intervention received on outcomes.

A preliminary cost-effectiveness analysis is performed with the baseline measurement as control condition from a healthcare perspective. The healthcare costs per individual participant are calculated by multiplying resource use (e.g., doctor appointments, hospital admissions) with corresponding unit prices if available. Utility values are calculated using the EuroQol 5-level EQ-5D (EQ-5D-5L) to estimate the quality-adjusted life years (QALYs) [27]. EQ-5D-5L has demonstrated good measurement properties such as ceiling effects, reliability, and sensitivity [42].

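### Randomisation is optional and varies by site, and where areas define the arms unblinded local recruiters may know the arm before selection, consent and T0; the pooled estimate does not separate these sites

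*Protocol article*

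**What the plan says.** Allocation. Protocol article, Study population and eligibility: "Study sites might apply randomization at individual or cluster level to create intervention and control condition". Study design describes the whole as follows: "A controlled trial is performed with an intervention condition and a control condition". The article does not say which site uses which method, or how arms are formed at a site that does not randomise.

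Recruitment. Under Study design, local organisations "or the local research team, depending on study site, select eligible individuals". The same section continues: "Potential participants in the catchment area of an intervention or control site receive information about the study and an invitation to provide informed consent". Under Study population and eligibility: "The research assistant recruits potential participants in collaboration with local agencies that work in the catchment area".

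Eligibility. On the energy poverty criterion: "Together they determine energy poverty conditions (criterion iii), based on their knowledge of and experience with the target population". The four EPOV indicators serve as a guideline for this judgement.

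Blinding. Study design: "Study participants, intervention providers and research assistants are not blinded due to the nature of the intervention".

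Analysis. Data management and analysis combines all sites, uses multilevel regression and repeats the analyses for each site. It adds: "Analyses are performed according to the ‘intention to treat’ principle". It does not separate sites by allocation method. Power consideration treats the trial as 12 clusters, one per arm per site. Limitations says that questionnaire variables will be used to control for differences between arms, and concedes that confounding may remain.

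**The concern.** Three features act together. The allocation rule is optional, the invitation is tied to an area that is already labelled intervention or control, and entry rests on the judgement of staff who are not blinded. Where areas define the arms, recruiters can know which arm they are filling when they decide whom to approach and who counts as energy poor.

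Other parts of the protocol give them, and the people they invite, reasons to decide differently by arm:

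- One exclusion is inability to take part in the site's intervention actions. That judgement bears more naturally on people who will receive those actions.
- Only the intervention arm has monthly health measurements and home sensors.
- Controls may be offered incentives, and at some sites a place on a waitlist. If the arm is known at invitation, people are consenting to different offers.

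The main outcome, EQ-5D-5L, is self-reported, so T0 answers given with the arm known may also be affected.

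Selection after the arm is known can bias even a site whose areas were properly randomised. At stake is whether a difference in the pooled estimate reflects the programme or partly reflects who was enrolled.

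**Working it through.** **Inputs** (Power consideration): 700 per arm after 20% loss from 875; cluster size 117; ICC 0.02; alpha 0.05, taken as two-sided; power 0.80; stated detectable difference 0.28 SD.

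**The plan's own figure**

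- Design effect = 1 + (117 − 1) × 0.02 = 3.32.
- Pooled SE = √(2 × 3.32 / 700) = 0.097 SD.
- Detectable difference = (1.960 + 0.842) × 0.097 = 0.273 SD.

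This agrees with the stated 0.28, which is slightly conservative. The pooled SE is used below.

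**What a selection bias would do.** The document gives no figure for the bias. I assume 0.10 SD at each affected site, which is 0.10 / 0.28 = 36% of the stated detectable difference. For scale, with an ICC of 0.02 the difference between two independent areas has an SD of √(2 × 0.02) = 0.20 SD. The design effect already allows for that random variation. Selection by recruiters would come on top of it.

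With sites weighted equally, the pooled shift is 0.10 × (affected sites / 6). If the programme has no effect, the two-sided rejection rate is 1 − Φ(1.96 − shift/SE) + Φ(−1.96 − shift/SE).

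| Setting | Shift (SD) | SE (SD) | Shift/SE | False-positive rate |
|---|---|---|---|---|
| Pooled, 3 of 6 sites affected | 0.05 | 0.097 | 0.51 | about 8% |
| Pooled, all 6 affected | 0.10 | 0.097 | 1.03 | about 18% |
| One site, 100 per arm, ICC 0.02 | 0.10 | 0.244 | 0.41 | about 7% |
| One site, 100 per arm, no clustering | 0.10 | 0.141 | 0.71 | about 11% |

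The 100 per arm is the minimum of 125 less 20%. For the third row, the design effect is 1 + 99 × 0.02 = 2.98 and SE = √(2 × 2.98 / 100) = 0.244. For the fourth, SE = √(2 / 100) = 0.141.

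With three of six sites affected and an assumed bias of 0.1 to 0.3 SD, the pooled shift is 0.05 to 0.15 SD and the rate is about 8% to 34%.

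**The case against.** **Is the arm known before consent everywhere?** A reader might infer so. The documents do not support that. It is an inference from the invitation sentence. The eligibility section has people enrolled on consent and each site allocating a number to each condition, which fits allocation after consent at a site that randomises individuals. The blinding statement concerns the trial as a whole and does not say what staff know at screening. This objection stands, and it limits the point to sites where areas define the arms.

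**Can the programme effect then not be told from selection at all?** That is also too strong. Analyses are repeated by site, so a reader who knows each site's method can compare them. The main outcome is a change from T0, which removes part of a stable baseline difference. It does not remove a difference in expected course, and T0 itself may have been answered with the arm known.

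**The authors do not claim a randomised trial.** They call it a controlled trial and a pre-post controlled design, and Limitations concedes confounding. This stands. But questionnaire covariates cannot fully correct for selection on what recruiters know privately, and Limitations mentions neither mixed allocation nor unblinded selection. Intention to treat can simply mean analysis as assigned, so that wording is no error.

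**Uniform clustering in the power section is harmless.** Correct. If some sites randomise individuals, the assumption is conservative: with equal site weights the detectable difference is 0.273 SD if none do so, 0.220 SD if three do and 0.150 SD if all six do. The point is about bias, not power.

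**The article is condensed.** Each site's method may be set out in the full protocol, and an analysis plan could add results by allocation method. Neither can restore concealment once people have been enrolled with the arm known.

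**Conclusion.** The concern holds for sites where areas define the arms. Followed as written, the plan lets arm-aware, unblinded recruiters make a discretionary eligibility judgement there, and it pools those sites with any randomised ones. The stated safeguards, covariate control and site-by-site analyses, reduce the problem without removing it.

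The size is not computable from the document. The rates of about 8% (three sites affected) and about 18% (all six) rest on an assumed bias of 0.10 SD, equal site weights and the protocol's own design effect. For a single site the same assumption gives about 7% with the protocol's ICC and about 11% without clustering. These figures show what a modest bias could do; they do not estimate what will happen. The change should be made before recruitment starts.

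**What to change.** 1. Where a site randomises, complete eligibility, consent and T0 before the allocation is drawn or disclosed. Where areas are pre-assigned, take T0 before arm-specific programme details are given.
2. Apply the same EPOV-based entry criterion in both arms, and record for each enrolled participant which indicators were met.
3. Report the effect for randomised and for non-randomised sites separately beside the pooled estimate. Word conclusions from non-randomised sites as subject to confounding.

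Cost: mainly a change in the order of steps, a short screening record and one further analysis. Energy poverty indicators and energy spending are already collected at baseline in both arms. However, the low-expenditure and high-share EPOV indicators need expenditure and income data at screening, to compare with national medians. Pre-assigned areas cannot fully conceal the arm, and the separate estimates will be less precise than the pooled one.

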### Data collection

Data are collected using complementary methodology: self-reported questionnaires on health, wellbeing, household energy expenditure and consumption, health monitoring (e.g. blood pressure measurements), household data from sensors, and qualitative data on the lived experience of the intervention. A data platform, established prior to the start of the study, will support data collection and integration of data from different sources.

#### Data collection in both study arms

Individual level data on health, wellbeing and energy-poverty indicators in both research groups are collected through questionnaires completed by the participating adults (self-report). The questionnaires can be completed on paper or digitally through a secured mobile or web-based application. Instruments for which no validated translations are available will be translated (forward and backward translations). Before the start of the study, the questionnaire is pilot-tested to ensure its user-friendliness in terms of appropriateness, comprehensibility and length.

Instruments and variables collected in both study arms are presented in Table 2.

**Table 2 Tab2:** Instruments and variables collected in both study arms

Variable	Instrument/indicator	Data source	Timeline
**Sociodemographic details: age, sex, gender, occupation, etc**	Ad-hoc questionnaire	Online/offline self-reported questionnaire	Baseline
**HEALTH AND WELLBEING MEASURES**			
**Quality of life**	EQ-5D-5L [27]	Online/offline self-reported questionnaire	Baseline, 6, 12 and 18 months
**Mental health: depression, anxiety, stress**	Depression Anxiety Stress Scales 21 (DASS-21) [28]		
**Frailty**	Self-Administered Multidimensional Prognostic Index Short Form (SELFY-MPI-SF) [29]		
**Subjective comfort in households**	European Statistics on Income and Living conditions survey (EU-SILC) [30]		
**Comorbidities**	International Consortium for Health Outcomes (ICHOM) Overall Adult Health set [31]		
**Lifestyle behaviour: Body Mass Index (BMI), alcohol consumption, smoking status**	ICHOM Overall Adult Health set [31]		
**Lifestyle behaviour: Physical activity**	One item of the Internal Physical Activity Questionnaire (IPAQ) [32]		
**Loneliness**	University of California, Los Angeles (UCLA) 3-item Loneliness Scale [33]		
**Control over life and social support**	Adult Social Care Outcomes Toolkit [34]		
**Health care use**	Self-management resource center (SMRC) Health Care Utilization questionnaire [35]		
**Decompensation of chronic disease**	Number of diagnosed exacerbations, all health settings (emergencies, acute units, hospitalization, primary care)	Online/offline self-reported questionnaire (if available, direct extraction from Electronic Health Records)	Baseline, 6, 12 and 18 months
**Readmissions**	Admissions to the emergency department, acute units or regular hospitalisation		
**Use of primary attention services**	Visits to the primary attention services distinct from those aimed at renewing the prescriptions		
**ENERGY POVERTY RELATED MEASURES**			
**Energy poverty indicators**	European Statistics on Income and Living conditions survey (EU-SILC) [30]	Online/offline self-reported questionnaire	Baseline, 6, 12 and 18 months
**Attitudes/coping**	Self-reported scale, three items of the European Social Survey [36], two items of the Climate Change Worry Scale [37]	Online/offline self-reported questionnaire	
**ENERGY EFFICIENCY EVALUATION**			
**Energy consumption**	On grid (e.g. electricity, gas, heat) and off-grid (e.g. bottled gas, coal) energy consumption	Online/offline self-reported questionnaire, if possible, smart meters or energy provider	Baseline, 6, 12 and 18 months
**Household income spent on different sources of energy**	% of income/Euros	Online/offline self-reported questionnaire and, if possible, energy provider	

The main outcome is the change in health-related quality of life (HrQoL). This is measured by the EuroQol 5-level EQ-5D (EQ-5D-5L) instrument [27]. Secondary outcome measures include satisfaction with life, mental health, outcomes related to lifestyle behaviour, comorbidities, loneliness, subjective comfort in households, control over life, and social support. Frailty is assessed in older adults. Energy-related outcome measures are energy poverty indicators as defined by EPOV [26], attitudes towards adoption of energy efficiency measures, and coping behaviours.

Additional data on health care use are collected through electronic health records (when possible) for both intervention and control condition. This entails visits to the emergency ward and relevant care use outcomes. If data is not available through the electronic health records this information is obtained in the self-reported questionnaire.

Household spending on energy and energy consumption is obtained for participants in the intervention and control condition via the self-reported questionnaire. Depending on the study site additional data may be collected via smart energy meters or via energy providers.

#### Data collection in intervention condition

In the intervention condition, additional data will be collected through health monitoring. Peak flow, oxygen saturation (SpO_2_), blood pressure and heart rate are measured every month through the use of health monitoring devices. Devices, such as Fitbit-like trackers, send health data to the data platform directly. In other instances, data is obtained manually during a home visit. Peak flow and SpO_2_ are measured in a resting position and after a six minutes’ walk. Blood pressure and heart rate are measured three times in a resting position with a three-minutes interval. Sleep quality is measured with the Pittsburgh Sleep Quality Index with a three-month interval [38].

Home sensors collect household data on temperature, humidity, and air quality in the intervention condition. Data are collected near real-time.

Qualitative interviews are conducted in each study site with 20 subjects of the intervention to evaluate the impacts of the intervention and to help explain findings. The qualitative research is longitudinal: the first interview takes place after the project has started, and the second when the project is finished. Participants are asked in the baseline questionnaire if they are willing to be involved in the qualitative part of the study. From these volunteers, the baseline questionnaire results are used to construct a sample which reflects the diversity of the main groups identified. Specific attention is paid to ensuring a gender-balanced sample, and to including people who report a range of health and energy poverty experiences. General guidelines for the set-up of the interviews are designed collaboratively across the research team, and training and support in implementation is offered by the lead qualitative partner. Study partners conduct interviews in their study sites and collect qualitative data from the studys’ participants following a consistent but adaptable methodology. Key topics in interviews include the participant’s experience of their home and energy use in the home, their coping strategies in the home, the wider effects of energy poverty and the impacts of the intervention.

Instruments and variables collected in the intervention condition are presented in Table 3.

**Table 3 Tab3:** Instruments and variables collected in intervention arm

Variable	Instrument/indicator	Data source	Timeline
**Respiratory & cardiovascular function indicators**	Peak flow	Internet of Things (IoT) home health control devices	Monthly (30 days)
	SpO_2_		
	Blood pressure		
	Pittsburgh Sleep Quality Index [38]		Every 3 months
**Household conditions: temperature**	Celsius Degree	IoT DT home sensors	Real time monitoring
**Household conditions: humidity**	% Relative humidity		
**Household conditions: air quality**	CO_2_ and CO concentration		
**Qualitative interviews**	Impressions, comments, experience and subjective perceptions captured in focus groups and interviews & codified	Qualitative analysis codified records	3–6 months, 12–15 months

